### **5.3.3 Other Supplies**

In addition to drug and placebo for the study, the study center will also be provided sterile syringe filters, amber colored bag covers (with tamper evident tape) and amber colored

infusion tubing sets. See the Pharmacy Manual for the specifications and details regarding these ancillary supplies.

## 5.4 Overdose Management

An overdose is any dose of study treatment given to a subject or taken by a subject that exceeds the dose described in the protocol. Any overdose, with or without associated AEs, must be promptly reported to the managing CRO, CTI and Galectin Therapeutics.

- **SAE [contact]**
- **SAE eFax line: [name]**
- **eFax email: [[contact]](mailto:[contact])**

Overdoses without signs or symptoms do not need to be recorded as AEs; in case of any AEs associated with the overdose, these should be reported on relevant AE/SAE sections in the CRF.

### 5.4.1 Treatment of Overdose

There are no known or anticipated adverse effects of GR-MD-02 overdose. The subject should be observed, but there are no specific therapies to be instituted.

### 5.4.2 Medication Errors

A medication error is any unintentional error in prescribing, dispensing, or administration of the study drug. The study drug is being prepared and administered at the study center by trained personnel, thereby reducing the risk of medication errors.

Acceptable treatment windows for infusions will be  $\pm 3$  days. Infusions given outside of accepted windows would be considered “out of window” doses. If a dose is out of window, the subject should be brought back into compliance with their visit dosing schedule. The subject should not dose within 7 days of the previous or next dose unless the medical monitor is consulted.

Any AEs resulting from medication errors will be recorded as AEs in the CRF.

### **5.4.3 Treatment of Medication Errors**

Should a medication error occur, the subject should be observed; but there are no specific therapies to be instituted.

### **5.5 Misuse for Illegal Purposes**

GR-MD-02 does not have known effects that may be addictive and there are no other reasons for misuse.

### **5.6 Blinding**

The aqueous solution of GR-MD-02 is a light yellow-tan color. It has not been possible to match the color with a placebo formulation. Therefore, the study pharmacist at each study center will be unblinded in the preparation of IMP for infusion. The formulated 10-mL solutions will be prepared for infusion as specified in the Pharmacy Manual in IV bags and placed in amber colored IV bag covers with amber colored tubing and infusion sets. The amber colored bags will be sealed with tamper evident tape. Placebo and drug solutions to be administered in the IV infusion set up are indistinguishable. Thus, the study subjects, primary investigators, and medical personnel will be blinded to whether the subject is receiving study drug. Infusion of the study drug causes no local reaction in animal studies or in humans participating in the Phase 1 clinical study and, therefore should not affect blinding.

#### **5.6.1 Breaking the Blind**

A subject's treatment assignment will not be broken until the end of the study unless medical treatment of the subject depends on knowing the study treatment the subject received. In the event that the blind needs to be broken because of a medical emergency, the investigator may unblind an individual subject's treatment allocation. As soon as possible, the investigator should first contact the medical monitor to discuss the medical emergency and the reason for revealing the actual treatment received by that subject. The treatment assignment will be unblinded by the investigator through the blinding code held by CTI. Reasons for treatment unblinding must be clearly explained and justified in the CRF. The date on which the code was broken together with the identity of the person responsible must also be documented.

## **5.7 Treatment Compliance**

Subject compliance will be determined by infusion records.

Acceptable windows for study drug dosing are  $\pm 3$  days. Infusions given outside of accepted windows would be considered “out of window” doses. If a dose is out of window, the subject should be brought back into compliance with their visit dosing schedule. The subject should not dose within 7 days of the previous or next dose unless the medical monitor is consulted.

## **5.8 Prior and Concomitant Therapy**

Use of all concomitant medications will be recorded in the subject’s CRF. The minimum requirement is that drug name, reason for use, dose, and the dates of administration are to be recorded. This will include all prescription drugs, herbal products, vitamins, minerals, and over-the-counter (OTC) medications. Any changes in concomitant medications also will be recorded in the subject’s CRF.

All prior treatments for liver cirrhosis and NASH will be recorded in the CRF. All other concomitant medications taken from 30 days prior to screening and throughout the entire duration of the subject’s time on study, will be collected in the CRF. Concomitant medications are defined as medications taken any time after the start of exposure to IMP. Prior medications are defined as medications discontinued prior to the start of exposure to study drug.

Any concomitant medication deemed necessary for the welfare of the subject during the study may be given at the discretion of the investigator. It is the responsibility of the investigator to ensure that details regarding the medication are recorded in full in the CRF.

## **5.9 Prohibited Medications or Therapies**

None.

## **6 Study Assessments and Procedures**

Before any study procedures are performed, all potential subjects will sign an ICF. Subjects will have the opportunity to have any questions answered before signing the ICF. The investigator must address all questions raised by the subject. The investigator will also sign the ICF.

The schedule of events for randomization, treatment phase, and follow-up in section 11.

### **6.1 Study Visits**

#### **6.1.1 Screening Visit (Week -6 to Day 0)**

Patients with a liver biopsy with NASH with Brunt Stage 3 fibrosis may enter screening. The screening visit window is up to 6 weeks prior to randomization. Subjects who fail to meet eligibility criteria within this 6-week period due to an abnormal laboratory result may undergo retesting of the abnormal laboratory parameter during the screening window and at the discretion of the investigator and with prior approval of the medical monitor. During the screening visit, the following information will be collected:

- Inclusion/exclusion criteria
- Medical, surgical, and medication history (concomitant medications taken from 30 days prior to screening)
- Collect demographic information
- 12-lead ECG
- Hematology
- Blood chemistry, including alpha-2 macroglobulin
- Coagulation profile
- Viral hepatitis B and C serology

- HIV serology
- Urinalysis
- Serum pregnancy test (females of childbearing potential only)
- Complete physical examination (including height [in cm] and weight [in kg]) with particular attention to examination for stigmata of liver disease/cirrhosis
- Vital sign measurements (including heart and respiratory rate, blood pressure, and body temperature)
- AE monitoring

## **6.1.2 Treatment Phase**

### **6.1.2.1 Randomization**

Randomization must occur within 6 weeks after screening has begun.

Prior to infusion Visit 1, subjects who meet the inclusion and exclusion criteria will be randomly assigned (1:1) placebo or GR-MD-02 in a dose of 8 mg/kg lean body mass.

### **6.1.2.2 Two Weeks Prior to Infusion Visit 1**

The following will be conducted within 2 weeks prior to the first infusion:

- LiverMultiScan
- MR-Elastography
- FibroScan

**6.1.2.3 Infusion Visit 1 (Week 1), Infusion Visit 2 (Week 3  $\pm$  3 days),  
Infusion Visit 3 (Week 5  $\pm$  3 days), Infusion Visit 4 (Week 7  
 $\pm$  3 days), Infusion Visit 5 (Week 9  $\pm$  3 days), Infusion Visit 6  
(Week 11  $\pm$  3 days), Infusion Visit 7 (Week 13  $\pm$  3 days), Infusion  
Visit 8 (Week 15  $\pm$  3 days), Infusion Visit 9 (Week 17  $\pm$  3 days)**

The following procedures and assessments will be conducted prior to administration of study drug:

- Limited physical examination (including weight, heart, lung and abdominal examination)
- Vital sign measurements (including heart and respiratory rate, blood pressure, and body temperature)
- Hematology, blood chemistry-including alpha-2 macroglobulin, and urine pregnancy test (Visit 1, 5 and 9 only)
- ECG (Visit 9 only)

The following information will be collected after study drug administration:

- AE monitoring
- Concomitant medications

**6.1.3 Follow-up study evaluations (7-21 Days after Final Dose)**

Within 7 to 21 days after the final 9th dose of IMP or where feasible following study termination, the following information will be collected:

- LiverMultiScan
- MR-Elastography
- FibroScan

### **6.1.4 Follow-up/Early Termination**

30 days after the last infusion visit the following information will be collected:

- Limited physical examination (including weight, heart, lung and abdominal examination)
- Vital sign measurements (including heart and respiratory rate, blood pressure, and body temperature)
- AE monitoring
- Concomitant medications

## **6.2 Efficacy Assessments**

### **6.2.1 LiverMultiScan**

LiverMultiScan® is a new method developed by Perspectum Diagnostics™ which is a novel magnetic resonance (MR) protocol that can be performed without intra-venous contrast on existing scanners. MR methods are ideally suited for tissue characterization as they can sample the entire liver quickly, and are safe, reproducible, and widely available. Using multiparametric MR, investigators were able to objectively quantify hepatic fibrosis, steatosis and hemosiderosis, an important step towards a safer alternative to liver biopsy (9). MR data will be evaluated by Perspectum Diagnostics™ and the cT1 generated as the primary endpoint for evaluation, which correlates with the degree of inflammation and fibrosis in the liver. LMS will be obtained following at least a 6 hour fast, including water.

### **6.2.2 MR Elastography**

MR elastography is a method for evaluating the stiffness of the entire liver using an electromechanical pulse and magnetic resonance imaging, and has been demonstrated to be useful in the evaluation of NASH with advanced fibrosis (8). MRE will be obtained at the same time as LMS. The procedure will be performed on Siemens 1.5 Tesla X 2 and 3.0 x 1 machines under the direction of [name], an experienced radiologist. Blinded paired MR-E exams from prior to randomization and at the end of the study will be evaluated [name].

### **6.2.3 FibroScan**

FibroScan is an FDA approved, non-invasive diagnostic instrument that uses an electromechanical vibrator and pulse-echo ultrasound to evaluate the elastic shear wave in liver tissue which is a measure of liver stiffness. The stiffness of the liver is recorded as the pressure measurement of kiloPascals. The stiffness of the liver correlates with the degree of liver fibrosis as assessed by liver biopsy, including subjects with NASH (10). One advantage of this method is that the volume of liver tissue assessed is ~100-times greater than volume assessed by liver biopsy. As such FibroScan represents a promising non-invasive, outpatient method for measuring changes in liver fibrosis over time. FibroScan evaluations will be performed after an 8 hour fast according to the manufacturer's instructions.

## **6.3 Safety Assessments**

All subjects receiving any part of at least 1 infusion of study treatment will be evaluated for safety. Safety assessments will include incidence of AEs during study treatment, emergent physical examination abnormalities, emergent vital sign and ECG abnormalities, and laboratory parameter abnormalities.

### **6.3.1 Vital Signs**

Vital sign measurements (including heart and respiratory rate, blood pressure and body temperature) will be collected before administration of IMP at time points specified in the schedule of assessments. Blood pressure will be obtained with the subject in the supine position and measured twice consecutively with a 1-minute interval between measurements. The average of the 2 measurements will be recorded.

### **6.3.2 Physical Examination**

A complete physical examination, including height and weight, will be performed at screening, with particular attention to examination for stigmata of liver disease/cirrhosis. A limited physical examination will only include weight, heart, lung, and abdominal examination according to the time points specified in the schedule of assessments.

### **6.3.3 Electrocardiogram**

A standard 12-lead ECG will be performed according to the schedule of events. Twelve-lead ECGs will be systematically digitally recorded after the subject has been in the supine position for at least 10 minutes. The electrodes will be positioned in the same location for each ECG recording. Electrocardiograms will be recorded before blood sampling.

### **6.3.4 Adverse Events**

#### **6.3.4.1 Definitions of Adverse Events**

The investigator is responsible for reporting all treatment-emergent AEs (TEAEs) that are observed or reported during the study, regardless of their relationship to IMP or their clinical significance.

An AE is defined as any untoward medical occurrence in a subject enrolled into this study regardless of its causal relationship to IMP. Subjects will be instructed to contact the investigator at any time after randomization if any symptoms develop.

A TEAE is defined as any event not present before exposure to IMP or any event already present that worsens in either intensity or frequency after exposure to IMP.

An SAE is defined as any event that results in death, is immediately life threatening, requires inpatient hospitalization or prolongation of existing hospitalization, results in persistent or significant disability/incapacity, or is a congenital anomaly/birth defect. Important medical events that may not result in death, be life threatening, or require hospitalization may be considered SAEs when, based upon appropriate medical judgment, they may jeopardize the subject or may require medical or surgical intervention to prevent one of the outcomes listed in this definition. Examples of such medical events include allergic bronchospasm requiring intensive treatment in an emergency room or at home, blood dyscrasias or convulsions that do not result in inpatient hospitalization, or the development of drug dependency or drug abuse.

#### **6.3.4.2 Eliciting and Documenting Adverse Events**

All AEs (serious and non-serious) will be assessed beginning at screening and up to 42 days after the last dose of IMP.

Serious AEs that occur more than 42 days after the last dose of IMP need not be reported unless the investigator considers them related to IMP.

At every study visit, subjects will be asked a standard nonleading question to elicit any medically related changes in their well-being. They will also be asked if they have been hospitalized, had any accidents, used any new medications, or changed concomitant medication regimens (both prescription and OTC medications).

In addition to subject observations, AEs identified from any study data (e.g., laboratory values, physical examination findings, ECG changes) or identified from review of other documents that are relevant to subject safety will be documented on the AE page in the CRF.

### **6.3.4.3 Reporting Adverse Events**

All AEs reported or observed during the study will be recorded on the AE page in the CRF. Information to be collected includes drug treatment, dose, event term, time of onset, investigator-specified assessment of severity and relationship to IMP, time of resolution of the event, seriousness, any required treatment or evaluations, and outcome. Adverse events resulting from concurrent illnesses, reactions to concurrent illnesses, reactions to concurrent medications, or progression of disease states must also be reported. All AEs will be followed to adequate resolution. The Medical Dictionary for Regulatory Activities (MedDRA, Version 17.1) will be used to code all AEs.

Any medical condition that is present at the time that the subject is screened but does not deteriorate should not be reported as an AE. However, if it deteriorates at any time during the study, it should be recorded as an AE.

Any AE that meets SAE criteria (Section 6.3.4.1) must be reported to the sponsor (designee) immediately (i.e., within 24 hours) after the time study center personnel first learn about the event.

Study personnel should complete the AE CRF, designating the event as serious.

#### **6.3.4.4 Assessment of Severity**

The severity, or intensity, of an AE refers to the extent to which an AE affects the subject's daily activities. The intensity of the AE will be rated as mild, moderate, or severe using the following criteria:

- Mild: These events require minimal or no treatment and do not interfere with the subject's daily activities.
- Moderate: These events result in a low level of inconvenience or concern with the therapeutic measures. Moderate events may cause some interference with normal functioning.
- Severe: These events interrupt a subject's usual daily activity and may require systemic drug therapy or other treatment. Severe events are usually incapacitating.

Changes in the severity of an AE should be documented to allow an assessment of the duration of the event at each level of intensity to be performed. Adverse events characterized as intermittent do not require documentation of onset and duration of each episode.

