**Statistical Methods:**

All statistical tests will be two-sided and will be at the 5% level of significance. Unless otherwise specified, continuous variables will be summarized by randomized treatment group with the number of non-missing observations, mean, standard deviation, median, 25th and 75th percentile displayed. Categorical data will be summarized by randomized treatment group as counts and percentages.

Analysis of the primary and secondary efficacy endpoints will be based on the ITT analysis set. Supportive sensitivity analyses of these endpoints will be performed using the Per Protocol analysis set, treated subjects with no major protocol deviations.

The primary efficacy endpoint analysis is the baseline-adjusted change in cT1 score at following treatment for 16 weeks with placebo as compared to subjects treated with GR-MD-02 (8 mg/kg/week). Change in cT1 as determined by LMS from baseline will be compared between treatment groups using analysis of covariance adjusted for baseline cT1 score at screening. Secondary endpoints will be analyzed in a similar fashion.

All subjects receiving any part of at least one injection of study treatment will be evaluated for safety, including evaluation of the incidence of treatment-emergent adverse events, Grade 3 or greater adverse events, serious adverse events and adverse events leading to discontinuation of study treatment. Laboratory and vital signs assessments will be evaluated over time on study using descriptive statistics. Shift analyses of relevant clinical laboratory parameters will be produced showing shifts across low, normal, and high categories.

A total sample size of 30 patients will be enrolled in the two groups based on the following assumptions: 1) True mean change in cT1 from baseline of 0 in the placebo group; 2) true mean change in cT1 of 53 ms (milliseconds) from baseline in the GR-MD-02 dose group; 3) common standard deviation of 50 ms for difference in cT1; 4) null hypothesis,  $H_0: \theta = \Delta G - \Delta p = 0$ ; 5) type I error,  $\alpha = 0.05$  (two-sided significance test); 6) power = 80%; 7) statistical test = two-sample t-test for mean difference 8) randomization ratio = 1:1

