## **4.2 Withdrawal of Subjects From the Study**

The duration of the study is defined for each subject as the date signed written informed consent is provided through the last follow-up visit 30 days following the last drug infusion.

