### **7.8.4 Safety Analyses**

All subjects receiving any part of at least 1 infusion of study treatment will be evaluated for safety. The safety analyses will include evaluation of the incidence of treatment-emergent adverse events (TEAEs), Grade 3 or greater AEs, SAEs and AEs leading to discontinuation of study treatment using the Common Terminology Criteria for Adverse Events Version 4.0 or higher. Laboratory and vital signs assessments will be evaluated over time on study using descriptive statistics. Shift analyses of relevant clinical laboratory parameters will be produced showing shifts across low, normal, and high categories.

All heart rate (bpm), 12-lead ECG parameters, PR Interval (msec), QRS Interval (msec), QT Interval (msec), and QTc Interval (msec) will be measured, and overall interpretation will be summarized for all subjects by study visit including the last visit of the study.

Electrocardiogram parameters will be summarized using descriptive statistics. Mean and mean change from baseline values will be presented for every scheduled assessment. Change

from baseline will be calculated as the post-baseline measurement minus the baseline measurement. If either the baseline or post-baseline value is missing, the observation will not be included in the change from baseline summary. In addition, counts and percentages for ECG overall interpretation (normal, abnormal, clinically significant, and not clinically significant) will be presented for each scheduled assessment.

For physical examinations, the results (normal, abnormal, or not done) by body system of the full physical examination at the randomization visit and follow-up visits will be summarized with descriptive statistics by treatment group and visit. For physical examinations performed at postrandomization time points, the number and percent of subjects with no change or any significant changes since the previous examination will be presented by treatment received. In addition, a shift table will be included to summarize the number and percent of subjects with changes from baseline to each postrandomization visit by body system for each treatment group. The number and percent of subjects with normal and abnormal results (clinically significant vs. not clinically significant) for each body system will be presented by treatment group.

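### The CTCAE Grade 3 or greater analysis has no matching severity item or mapping, and the 42-day adverse event window runs 12 days past the last scheduled evaluation

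*Protocol*

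**What the plan says.** **Severity.** Protocol Section 6.3.4.4 states: "The intensity of the AE will be rated as mild, moderate, or severe using the following criteria". The criteria turn on interference with daily activity and, to a lesser degree, on the need for treatment. Section 6.3.4.3, which lists what is recorded for each adverse event (AE), names one severity item: "investigator-specified assessment of severity and relationship to IMP". No numeric grade appears there.

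Section 7.8.4 plans to analyse "Grade 3 or greater AEs, SAEs and AEs leading to discontinuation of study treatment using the Common Terminology Criteria for Adverse Events Version 4.0", and its next words allow any later version. The synopsis, under Statistical Methods, repeats "Grade 3 or greater adverse events, serious adverse events and adverse events leading to discontinuation of study treatment" without naming a scale, and the synopsis entry on safety assessments does the same.

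**Time window.** Section 6.3.4.2 states: "All AEs (serious and non-serious) will be assessed beginning at screening and up to 42 days after the last dose of IMP". Section 4.2 defines each subject's time in the study as running from consent "through the last follow-up visit 30 days following the last drug infusion". Section 6.1.4 places the last AE monitoring at that visit: "30 days after the last infusion visit the following information will be collected". Table 11-2 puts the ninth infusion on Study Day 112 and the final visit, which carries the last AE evaluation, on Study Day 142 with a window printed as +3 days.

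**The concern.** The protocol fixes the severity scale to be collected and the severity scale to be analysed, and they are different scales. If the investigator is never asked for a CTCAE grade, the Grade 3 or greater table has to be built afterwards. One route is to treat severe as equivalent to Grade 3 or greater. The other is for someone other than the treating investigator to regrade events from the record. The first route changes what is counted, and the second brings in judgement after the event. Leaving the CTCAE version open adds a further choice.

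The protocol also fixes two time limits that disagree. An AE 35 days after the last dose lies inside the window of Section 6.3.4.2 and outside the subject's participation under Section 4.2. Section 6.3.4.2 ties its eliciting questions to study visits, and no visit follows the 30-day one. Events in that stretch therefore reach the database only if the subject volunteers them. For serious events, what the site must report is left unclear.

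**Working it through.** **Severity: the passages side by side**

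| Question | Sections 6.3.4.3 and 6.3.4.4 (collected) | Section 7.8.4 (analysed) |
|---|---|---|
| Scale | Three levels: mild, moderate, severe | CTCAE grades, threshold at Grade 3 |
| Basis | Effect on daily activity, with reference to treatment needed | CTCAE criteria |
| Version | Not applicable | 4.0 or any later version |
| Rule linking the two | None | None |

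1. Section 6.3.6 has clinically significant abnormal laboratory, ECG and vital-sign results recorded as AEs (laboratory findings explained by the underlying disease are excepted unless worse than expected). Such findings therefore enter the AE data.
2. Under Section 6.3.4.4, a finding that needs no treatment and does not disturb daily activity meets the definition of mild. A large, untreated, symptom-free laboratory change is thus mild on the collected scale.
3. If severe is set equal to Grade 3 or greater, that event drops out of the table, although a grade based on the laboratory value could place it there.
4. For clinical AEs, Section 6.3.4.3 does collect event term, treatment given, seriousness and outcome. These could inform a retrospective grade, but they are not an investigator's grade.

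**Time window: inputs and arithmetic**

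Inputs: last infusion on Day 112, final visit 30 days later and visit window +3 days (Table 11-2); AE window of 42 days after the last dose (Section 6.3.4.2).

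- Plan's own figure: 112 + 30 = 142. This reproduces the Day 142 printed in Table 11-2.
- End of the AE window: 112 + 42 = Day 154.
- Gap: 154 − 142 = 12 days. As a share of the post-dose window, 12/42 = 29%.
- Gap if the visit falls at the end of its window: 142 + 3 = 145, and 154 − 145 = 9 days.

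Both limits count from the last dose, so the 12 days do not depend on that dose falling exactly on Day 112. Section 3.1 also allows the final visit to take place at the time of early discontinuation. For such a subject, a final visit *x* days after the last dose leaves 42 − *x* days without a scheduled contact, which is more than 12 whenever *x* is below 30.

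**The case against.** A reader might infer that the safety analysis as a whole cannot be produced. The protocol does not support that. Section 7.8.4 also lists treatment-emergent AEs, serious AEs, AEs leading to discontinuation, laboratory and vital-sign summaries, shift tables, ECG and physical examination. All of these can be produced from what is collected. Grade 3 or greater is one line of the analysis list and is not named in the safety objectives (Section 2.4) or endpoints (Section 7.4).

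Nor is every symptom-free laboratory event mild whatever its size. The definition of mild also requires minimal or no treatment, and the definition of severe mentions systemic drug therapy, so the argument holds only for untreated findings. Hematology and chemistry are measured at screening and at infusions 1, 5 and 9, so wherever a CTCAE grade is a numeric limit on one of those tests it could be derived from the values. That objection stands for laboratory tests. It does not reach clinical AEs.

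The list in Section 6.3.4.3 is not worded as exhaustive, the CRF is not shown, and Sections 7 and 7.8 leave analysis detail to the SAP. A SAP could state a mapping. It could not supply investigator grades that were never recorded, and the two scales in the protocol would still disagree.

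On the window, a reader might infer that no information at all comes in after 30 days. Section 6.3.4.1 tells subjects to contact the investigator if symptoms appear after randomization, and Section 6.3.4.7 follows reported events to resolution. Capture is passive, not absent. Section 10.3 does not help the stronger reading, because it defines the end of the trial and not of a subject's participation. The safety endpoint is AEs while on treatment, no analysis in Section 7.8.4 is defined on the 42 days, and collection is the same in both blinded arms. The gap therefore blocks no analysis, and no bias between arms has been shown. The 29% is a share of days, not of events.

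**Conclusion.** Both contradictions stand, in limited form.

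- **Severity.** One planned analysis, the CTCAE Grade 3 or greater incidence, has no matching data item and no mapping. Laboratory grades could largely be recovered from measured values. Clinical AEs would need grading after the fact. A shortcut through the severe category would miss untreated, symptom-free laboratory AEs.
- **Window.** AE assessment is promised for 12 days (9 with the full visit window) beyond the last scheduled evaluation and the end of participation. In those days ascertainment rests on self-report, so counts for the period would be incomplete.

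This assumes that the CRF follows Section 6.3.4.3 and carries no separate grade, that CTCAE grades laboratory findings by value and not by effect on daily life (the protocol does not reproduce the criteria), and that the visit window is as printed. The number of events affected cannot be estimated from the protocol. The primary endpoint is not touched. The point should be corrected because safety is a stated objective and an investigator's grade not taken at the time cannot be reliably recovered later.

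**What to change.** (a) In Section 6.3.4.4 and on the AE CRF, record the CTCAE grade for every AE, laboratory AEs included, in one named version, and put the same version in Section 7.8.4. The three-level scale can stay as an additional field. Alternatively, restate the analysis in Section 7.8.4 and in both places in the synopsis on the scale actually collected.

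(b) Reconcile Section 6.3.4.2 with Sections 4.2 and 6.1.4 and Table 11-2 so that the AE window and the last scheduled AE contact coincide, whichever length the sponsor settles on. State how this applies when the final visit is held at early discontinuation. Use the same window for the treatment-emergent AE tables, because the definition in Section 6.3.4.1 has no end date.

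The cost is one CRF field and protocol wording. If the longer window is kept, add at most one telephone contact per subject.
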